Substudy 3: quasi-experimental single-arm pilot	Quasi-experimental, n=100 existing subusers	Within-person change in adherence and HbA_1c_ after OMNIdiasense-guided MI sessions	Feasibility, acceptability, and effect-size estimates for a future definitive trial.
Substudy 3: pilot RCT^k^ with appropriate reporting standards	Parallel 1:1, n=50 newly diagnosed (25 intervention, 25 control)	Between-group difference in CGM^l^ adherence at 12 months; secondary clinical, behavioral, and satisfaction outcomes	Generates the effect-size, recruitment, retention, and fidelity estimates required for a definitive multicenter trial.

^a^HbA_1c_: hemoglobin A_1c_.

^b^BP: blood pressure.

^c^RFT: renal function test.

^d^LFT: liver function test.

^e^BenCGM: Benefits of Continuous Glucose Monitoring Scale.

^f^BurCGM: Burden of Continuous Glucose Monitoring Scale.

^g^RSQ: Response to Stress Questionnaire.

^h^SEDM: Self-Efficacy for Diabetes Management Scale.

^i^PAID-Peds: Problem Areas in Diabetes-Pediatric version.

^j^PAQ-A: Physical Activity Questionnaire for Adolescents.

^k^RCT: randomized controlled trial.

^l^CGM: continuous glucose monitoring.

CGM distribution in Oman commenced in May 2024 following extensive capacity-building of diabetes clinic staff in 30 health facilities across all governorates. By February 2025, approximately 1500 children with T1DM had received CGMs, recorded centrally in the national Al Shifa health information system.

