### Substudy 2: Correlates of CGM Adherence: Cross-Sectional Mixed Methods Study

#### Design and Population

Substudy 2 is a cross-sectional mixed methods study using supervised face-to-face interviews with adolescents aged 10-18 years drawn from substudy 1. RMs will randomly sample participants from the Al Shifa–derived cohort. The dependent variable, pattern of CGM use, will be dichotomized as CGM optimizers (≥6 days/week) and CGM subusers (<6 days/week or discontinued), consistent with prior pediatric work [25].

Eligible participants will include children aged 10-18 years with T1DM who received CGM under the national initiative and whose primary caregiver consents. Children will be excluded if they are unable to complete the structured interview owing to severe cognitive or sensory impairment.

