### Substudy 3: Pilot Evaluation of OMNIdiasense

#### Design

Substudy 3 evaluates the AI-assisted assessment tool OMNIdiasense through 2 parallel components, both fed by an embedded AI model-development workstream described below.

Quasi-experimental single-arm pilot: 100 existing CGM subusers identified in substudy 2 receive OMNIdiasense assessment prior to CGM reintroduction, followed by MI-guided behavioral support delivered by a trained diabetic nurse within the routine pediatrics endocrine clinics.Pilot RCT: 50 newly recruited children with T1DM, randomized 1:1 to (1) intervention, OMNIdiasense assessment plus MI-guided support before CGM initiation or (2) usual care without exposure to the tool. Both arms receive CGM and standard clinical follow-up.

All 150 participants are followed for 12 months, with assessments at baseline, 3, 6, and 12 months. The flow of participants is presented in Figure 1.

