#### Sample Size

The pilot RCT sample size was based on the prevalence of optimal CGM use of approximately 50% [25] and a moderate effect (odds ratio 0.53) reported for adolescent CGM use. Using G*Power 3.1 (Heinrich Heine University Düsseldorf), at least 25 participants per arm are required to achieve 80% power at α=.05. The single-arm component (n=100) is powered for paired-sample within-person change in adherence and HbA_1c_.

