#### Inclusion and Exclusion Criteria

Quasi-experimental component: existing children with T1DM aged 10-18 years classified as CGM subusers in substudy 2; primary caregiver consents and child assents.

RCT component: newly diagnosed children with T1DM, aged 10-18 years, eligible for CGM under the national program, who have not yet received CGM. Exclusion: severe psychiatric or cognitive comorbidity precluding informed assent or interview participation.

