#### Data Analysis

Analyses will follow the intention-to-treat principle. Descriptive statistics will summarize baseline characteristics. Within-person change in the quasi-experimental arm will be analyzed with paired *t* tests, Wilcoxon signed-rank tests, or generalized estimating equations as appropriate. Between-group differences in the RCT will use *t* tests, chi-square tests, and mixed effects models with random intercepts for repeated measures. Multivariable linear and logistic regressions will explore predictors of adherence change. Missing data will be handled by multiple imputation under a missing-at-random assumption with sensitivity analyses. Prespecified subgroup analyses will examine age band (10-13 vs 14-18 years), sex, governorate (Muscat vs others), and insulin modality (multiple daily injections vs pump); any post hoc subgroup analyses will be flagged as exploratory. The pilot RCT report will follow the CONSORT (Consolidated Standards of Reporting Trials) 2025 extension for pilot and feasibility trials, and the interventional protocol adheres to SPIRIT (Standard Protocol Items: Recommendations for Interventional Trials)-AI 2025 (Multimedia Appendix 10).

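### The single-arm pilot cannot give an effect size for the definitive trial: its pre-post change mixes CGM re-supply, and possibly regression to the mean, with the tool and MI

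*Protocol article*

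**What the plan says.** All references are to the protocol article.

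- **Who enters.** Substudy 3, Inclusion and Exclusion Criteria: "existing children with T1DM aged 10-18 years classified as CGM subusers in substudy 2". Substudy 2, Design and Population, defines the class as "CGM subusers (<6 days/week or discontinued".
- **What they receive.** Substudy 3, Design: "100 existing CGM subusers identified in substudy 2 receive OMNIdiasense assessment prior to CGM reintroduction", followed by nurse-delivered MI support.
- **What is measured.** Table 1, single-arm row: "Within-person change in adherence and HbA_1c_ after OMNIdiasense-guided MI sessions". Table 2 schedules sensor-wear days per week from device records at baseline, 3, 6 and 12 months.
- **How it is analysed.** Substudy 3, Data Analysis: "Within-person change in the quasi-experimental arm will be analyzed with paired" *t* tests, Wilcoxon signed-rank tests or generalized estimating equations. No comparison group is named for this arm.
- **How it is sized.** Substudy 3, Sample Size: "The single-arm component (n=100) is powered for paired-sample within-person change in adherence and HbA_1c". No effect size, SD, correlation, alpha or power is given for it.
- **What it is for.** Table 1, same row: "Feasibility, acceptability, and effect-size estimates for a future definitive trial".

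The RCT row of Table 1 also promises an effect size for a definitive trial. Anticipated Principal Findings and Future Directions both tie that trial to the between-group difference in adherence.

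**The concern.** An effect size for planning a trial should estimate what the intervention adds over what would have happened without it. The single arm cannot supply that, for two reasons.

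First, reintroduction of the sensor and MI reach the same children together. A child who has discontinued has zero wear, so having a sensor again can only raise it, whatever the tool or the nurse contributes.

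Second, entry depends on a low value of the variable whose change is then tested. If that same value is the starting point, ordinary within-child fluctuation pushes the mean upwards.

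The RCT control arm does not repair this. It contains newly diagnosed children who have not yet received CGM, so it does not show what existing subusers would do when re-supplied without MI.

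At stake is what the arm may conclude. As Table 1 stands, a rise that owes something to re-supply, and perhaps to selection, would be reported as an effect size for the tool plus MI. Two sources of effect size, only one of them controlled, would also sit side by side in the same table.

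**Working it through.** **The plan's own figure.** The n=100 cannot be reproduced because none of its inputs are stated. Working backwards with a paired *t* test (two-sided alpha 0.05, 80% power, both assumed here), n=100 detects a mean change of about 0.28 SD of the within-child differences.

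**Re-supply.** Let *f* be the share discontinued at entry and *w* their mean wear once they have a sensor again, with no MI effect and the other children unchanged. The arm mean then rises by *f* × *w*. The document gives neither quantity, so these are assumptions:

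- *f* = 0.20, *w* = 3: 0.20 × 3 = 0.6 day/week
- *f* = 0.30, *w* = 4: 0.30 × 4 = 1.2 days/week
- range over *f* = 0.10 to 0.50 and *w* = 2 to 5: 0.10 × 2 = 0.2 up to 0.50 × 5 = 2.5 days/week

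The choice of baseline does not remove this. A discontinued child measured afresh before the first MI session still starts at zero.

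**Regression to the mean, classification value used as the pre value.** Assumptions: wear on 0 to 7 days follows a beta shape (parameters 3 and 0.85, which puts about 56% below 6), occasions are linked by a normal copula with correlation *r*, children are selected at <6 on the first occasion, and there is no true effect.

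| *r* | mean gain, days/week | SD of change | gain/SD | chance of p<0.05, n=100 |
|---|---|---|---|---|
| 0.5 | 0.44 | 1.46 | 0.30 | 85% |
| 0.8 | 0.18 | 1.02 | 0.17 | 40% |
| 0.9 | 0.09 | 0.75 | 0.12 | 21% |

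A second model uses the protocol's approximate 50% optimizer prevalence: bivariate normal wear with the lower half selected. The expected rise is (1 − *r*) × φ(0)/0.5 = (1 − *r*) × 0.798 SD. That is 0.40 SD at *r* = 0.5 and 0.08 SD at *r* = 0.9, with chances of p<0.05 of about 99% and 44%. The size depends on the model; the upward direction does not.

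**Regression to the mean, separate later baseline used.** In the beta model, with the same correlation between every pair of occasions, the gain from a fresh baseline is 0.00 day/week and the chance of p<0.05 is 5%, at each *r* above. If correlation fades with time, some bias returns. With selection-to-baseline correlation 0.71 and baseline-to-follow-up 0.5, the gain is 0.31 day/week; with 0.89 and 0.8 it is 0.16.

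**Which baseline applies.** Table 2 schedules a substudy 3 baseline for wear. No section says whether the paired analysis starts from that value or from the substudy 2 classification.

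**The case against.** The strongest reply is that the document never says the selection value is the starting value. Classification happens in substudy 2, with recruitment planned from June 2026. Substudy 3 recruitment follows in the fourth quarter of 2026, with its own wear baseline in Table 2. The natural reading is that this later baseline is used, and then regression to the mean largely disappears. That stands, and for this reason the figures in the table above are conditional. A reader might infer that the paired test will probably be significant with no effect at all. The document does not support that for regression to the mean.

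A reader might also infer that the definitive trial will be too small. That is not supported either: Anticipated Principal Findings and Future Directions say it is to be powered on the between-group difference, and Strengths and Limitations says pilot effect sizes need confirmation. What remains is a conflict, because the single-arm row of Table 1 offers an effect size for the same trial.

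It is also fair that the article mostly speaks of within-person change, labels the design quasi-experimental, and lists feasibility and acceptability, which are proper outputs of a single arm. The share discontinued and their later wear are unknown, and the text does not say that children wearing a sensor on fewer than 6 days/week had lost supply.

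None of this answers the re-supply point. It survives a fresh baseline, and the limitations do not mention it.

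**Conclusion.** The point holds in a bounded form. Following Table 1 as written would treat a change that includes re-supply, and possibly regression to the mean, as an effect size for the tool plus MI. The re-supply part follows from the design for any discontinued children enrolled. Its size cannot be computed from the document, and the 0.6 day/week example rests wholly on an assumed 20% discontinued and 3 days/week of wear.

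The regression part depends on an unstated choice. It is about 0.44 to 0.09 day/week (85% to 21% chance of p<0.05) for assumed correlations of 0.5 to 0.9 if the classification value is the pre value. It is about nil if the Table 2 baseline is used and correlation is stable.

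This is a defect in the stated use of the arm, not in running it, and it should be corrected before substudy 3 recruitment begins.

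**What to change.** 1. In Table 1, delete the effect-size use from the single-arm row. Keep feasibility and acceptability and, if wanted, variance and retention.
2. State that the planning effect size, with its confidence interval, comes from the randomised contrast only. This brings Table 1 into line with Anticipated Principal Findings and Future Directions.
3. In Data Analysis, state that the pre value is substudy 3 baseline wear, measured in a fixed window after classification and before the first MI session, and not the substudy 2 classification value.
4. Report change separately for children who had discontinued and for those with low wear.
5. Name re-supply and regression to the mean under Strengths and Limitations.

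The cost is wording, a defined baseline window for a measurement Table 2 already schedules, and slightly more analysis. The stated change will probably look less favourable. The randomised estimate from 25 per arm will be imprecise, so its interval must be shown.

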### Coordination and Workforce

A total of 11 regional research managers (RMs), senior pharmacists nominated by their respective directorates general of health services, will coordinate the project. Their responsibilities will include:

Facilitating data collection in alignment with substudy objectives.Supervising the local conduct of the project.Liaising with families and clinical teams.Coordinating with relevant departments and sections regionally.Resolving operational queries.

All RMs will receive standardized training on study assessment tools, ethical considerations, conflict resolution, and data protection prior to data collection.

A trial steering committee, comprising the principal investigators, 2 regional directorate representatives, an independent statistician, and a parent representative, will meet quarterly to oversee progress and protocol fidelity. An independent data monitoring committee (DMC) of 3 external members (a senior clinical practitioner, a biostatistician, and a quality officer) will review safety, recruitment, and data-quality reports every 6 months. The DMC will operate under a charter agreed upon before recruitment begins.

### Substudy 1: Characteristics and Glycemic Outcomes of Omani Children Receiving CGMs

#### Design and Population

Substudy 1 is a retrospective cohort analysis of all Omani children with T1DM who received CGM through the national rollout between July 2024 and February 2025 across the 11 governorates. The minimum analytic exposure window is 3 months of CGM use from baseline.

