### CGM in Children: Effectiveness, Adherence, and the Adolescent Gap

Pediatric T1DM trajectories vary by age at onset, genetics, and environment. Younger children may experience more aggressive forms of disease with rapid metabolic deregulation [11], and education for both children and caregivers is central to safe self-management as autonomy increases [12]. Long-term complications, including retinopathy, nephropathy, and cardiovascular disease, can begin during youth, and early-onset cohorts demonstrate distinct trajectories of risk [13].

Recent systematic and randomized evidence increasingly supports CGM in pediatric populations: Teo et al [14] confirmed glycemic improvements with CGM use across age strata; Laffel et al [15] demonstrated superiority of CGM over fingerstick monitoring in adolescents and young adults with elevated HbA_1c_; and Hilliard et al [16] showed parental confidence and satisfaction in young children using CGM. Yet, meta-analytic data continue to highlight cost, accessibility, and educational barriers that erode the population-level effect [17,18]. The 2024-2025 update of the International Society for Pediatric and Adolescent Diabetes (ISPAD) Clinical Practice Consensus Guidelines reaffirms that the effectiveness of real-time CGM in children and adolescents is directly related to the amount of sensor wear and that early initiation following diagnosis is associated with better glycemic outcomes [19].

Despite these advances, registry data show that only about 19% of adolescents in the United States T1D Exchange and 46% in the German/Austrian Diabetes Patienten Verlaufsdokumentation registry meet the previous pediatric HbA_1c_ target of <7.5% [20-22], and the targets have since been further tightened to <7.0% [23,24]. Messer et al [25] introduced the operational distinction between “CGM optimizers” (≥6 days/week) and “CGM subusers” (<6 days/week or discontinuation) and demonstrated that perceived benefit and burden of CGM are the strongest psychosocial predictors of consistent adolescent wear. More recent real-world analyses confirm that adherence is independently associated with HbA_1c_ reduction and lower health care use [26], and 2024-2025 work using the “Adherence Starts with Knowledge-12” questionnaire links pubertal stage, diabetes duration, parental involvement, and BMI SD score with low treatment adherence and worse metabolic control [27].

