#### Expected Outcomes

Primary outcomes of substudy 1 are (1) the population-level prevalence of CGM optimizer status at ≥3 months and (2) the pre-post change in HbA_1c_. Secondary outcomes are pre-post changes in weight, BMI, BMI *z* score, systolic and diastolic blood pressure, lipid panel, renal function test (RFT), and liver function test (LFT); regional variation across governorates; and identification of routinely captured clinical predictors of optimal use that will be carried forward to the AI model in substudy 3.

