#### Statistical Analysis

Descriptive statistics will be presented as frequencies, percentages, means, and SDs or medians and IQRs, as appropriate. Pre-post comparisons will use paired *t* tests or Wilcoxon signed-rank tests for continuous variables and McNemar tests for categorical variables. Differences across governorates will be evaluated with chi-square tests and ANOVA. Logistic regression will model predictors of optimal CGM use. Analyses will be performed in IBM SPSS Statistics (version 28) and R software (version 4.4; R Foundation for Statistical Computing). Reporting will follow STROBE (Strengthening the Reporting of Observational Studies in Epidemiology) guidelines (Multimedia Appendix 2).

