#### Measurements

The face-to-face interview will include the following components, administered in Arabic where validated translations are available (Multimedia Appendix 4). Questionnaires that require official approval from the original authors or involve payment or restricted use will be obtained accordingly. Components of the questionnaire include the following:

Demographics and diabetes management: age, gender, region, current insulin modality (multiple daily injections vs insulin pump), past or current CGM use, duration of CGM use; diabetes duration imported from substudy 1.BenCGM and BurCGM: 8-item Likert scales each, validated in adolescents aged 12-19 years [25,35]. Cronbach α will be reestimated in a pilot phase.RSQ-PD: 57-item adolescent-specific measure yielding 5 proportional coping/stress factors [36-38].SEDM: 10-item single-factor scale validated in T1DM adolescents 13-17 years [39,40].PAID-Peds: 20-item measure of diabetes distress in youth [41].PAQ-A, Arabic version [42].Short dietary history screener [43].Open-ended items: compliance with CGM, school and educational performance, barriers and facilitators, side effects, and recommendations.

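### Substudy 1's primary pre-post HbA1c change pools all CGM recipients whatever their diabetes duration, so any fall from starting insulin in recently diagnosed children is counted as post-CGM change

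*Protocol article*

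**What the plan says.** Under Substudy 1, Design and Population, the cohort is "all Omani children with T1DM who received CGM through the national rollout between July 2024 and February 2025". The only restriction concerns exposure: "The minimum analytic exposure window is 3 months of CGM use from baseline". Nothing is said about time since diagnosis or since insulin was started.

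Under Expected Outcomes for Substudy 1, "the pre-post change in HbA_1c" is the second of two primary outcomes. Weight, BMI and BMI z score changes are secondary.

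Under Statistical Analysis for Substudy 1, "Pre-post comparisons will use paired *t* tests or Wilcoxon signed-rank tests for continuous variables". There is no comparison group, and no stratification or adjustment by duration is stated. The one regression has a different outcome: "Logistic regression will model predictors of optimal CGM use".

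Two other places bear on who receives CGM. The Substudy 3 eligibility criteria describe the RCT population as "newly diagnosed children with T1DM, aged 10-18 years, eligible for CGM under the national program, who have not yet received CGM". The Introduction cites guidance that "early initiation following diagnosis is associated with better glycemic outcomes".

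The data needed to separate the groups are already collected. Measurements for Substudy 2 lists "diabetes duration imported from substudy 1", and Data Collection for Substudy 1 includes drug and treatment history before CGM and at 3 months or more after it.

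**The concern.** In a child given CGM at or shortly after diagnosis, the pre-CGM HbA1c may reflect disease that was untreated or only just treated. It then falls because insulin has been started, whether or not a sensor is worn. In a child with established diabetes, the same before-and-after difference carries no such component. The paired test averages the two kinds of change, and the result describes neither group well.

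The direction of the distortion is known: it makes the change after CGM look more favourable. Weight and BMI are exposed too, since weight can be regained once insulin starts. The Conceptual Background of Substudy 1 says these short-term results after CGM will inform clinical follow-up pathways and the variables used to train the prediction tool. The article's limitations mention missing routine data in Substudy 1 but not this mixing.

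**Working it through.** The protocol states no effect size, SD or power for the HbA1c outcome, so there is no figure of its own to reproduce. What follows shows how large the artefact could be.

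**Inputs**
- From the protocol: n of about 1500 (Table 1).
- Assumed: the share *f* of the cohort whose pre-CGM HbA1c was measured at or near insulin start; their mean fall *d* from starting insulin, in HbA1c percentage points; an SD of change of 1.5 to 2.0 points; and no effect of CGM.

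**Formulas**
- Artefact in the pooled mean change = *f* × *d*.
- Simple standard error = SD/√n: 1.5/√1500 = 0.039 and 2.0/√1500 = 0.052.
- Probability that the paired test declares a fall when CGM does nothing = Φ(*f·d*/SE − 1.96), with SE = √[(SD² + *f*(1−*f*)*d*²)/n] and SD = 1.5. With no artefact this is 2.5%.

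**Results for d = 3 points**

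| Share *f* | Artefact (points) | In simple SEs (SD 2.0 to 1.5) | P(significant fall), n = 1500 | Same, n = 1000 |
|---|---|---|---|---|
| 1% | 0.03 | 0.6 to 0.8 | 12% | 9% |
| 2% | 0.06 | 1.2 to 1.5 | 32% | 23% |
| 5% | 0.15 | 2.9 to 3.9 | 94% | 83% |
| 10% | 0.30 | 5.8 to 7.7 | over 99% | over 99% |

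Worked line for 5%: 0.05 × 3 = 0.15. The mixture SD is √(2.25 + 0.05 × 0.95 × 9) = 1.64, so SE = 1.64/√1500 = 0.042. Then 0.15/0.042 is about 3.55, and Φ(3.55 − 1.96) = 0.94.

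**Smaller falls:** 5% × 2 points gives 0.10 points and a 70% chance of a significant fall; 2% × 2 points gives 0.04 points and 17%; 1% × 1 point gives 0.01 points and 4%, which is negligible.

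**After separating the strata:** in the established-diabetes stratum *f* is 0 by construction, apart from any misclassification at the cut-off, so this artefact is 0.

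**The case against.** The strongest reply is that the cohort's composition is not shown. The eligibility text for newly diagnosed children belongs to an RCT that recruits from late 2026. It establishes that the program serves such children, not that many were among the recipients of July 2024 to February 2025, when a new scheme was supplying children nationally. Nor is the pre-CGM value defined: a child diagnosed some months before dispensing may already have had an HbA1c measured on insulin. Both points stand. They make the concern conditional and leave its size open.

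A reader might infer a share from the Introduction's figure of about 10.2% annual growth in T1DM, which over 8 months would be 1 − 1.102^(−8/12), or about 6% of the pool. That figure is not specific to children or to CGM recipients and cannot carry the argument. A reader might also infer that a spurious significant result is assured. It is not: at a share of 1-2% the artefact stays within about 1.5 standard errors. The number with both HbA1c values may also be below 1500.

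It can be said too that Substudy 1 is descriptive. It names a pre-post change, not an effect of CGM, and its anticipated findings concern uptake, subuse and regional variation. That is right, and the protocol should not be read as claiming that CGM caused the change. But a descriptive average over two different processes is still hard to interpret, and the stated use in follow-up pathways invites the reading. A further inference, that governorates with more new diagnoses would look more successful, has no support: the document neither says that diagnosis mix differs by governorate nor that HbA1c change is what is compared there.

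Finally, stratification might sit in an analysis plan that is not shown. The population, the primary outcome and the test are nevertheless stated here, and together they yield the pooled estimate.

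**Conclusion.** The concern holds in conditional form. As stated, the primary pre-post HbA1c analysis would count any fall from starting insulin as change after CGM, in a known direction and by an unknown amount. On the assumptions shown, the artefact runs from about 0.03-0.06 points at a share of 1-2%, which is hard to tell from noise, to 0.15-0.30 points at 5-10%, enough to make a significant fall likely with no CGM effect. Nothing in the document says which applies. The point merits a change because separating the groups uses data already in hand and would itself show whether the problem is trivial or large.

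**What to change.** Report the pre-post changes in HbA1c, weight and BMI separately for established and recently diagnosed diabetes, using the extracted duration and treatment history. Choose and justify one cut-off, for example 12 months of diabetes at first CGM dispensing. This is an analysis choice, the protocol supplies no such figure, and another justified value would serve. Then:

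- base any statement about change after CGM on the established stratum;
- describe the recent-diagnosis stratum as the course after diagnosis;
- show the all-comers estimate alongside, with the number in each stratum;
- keep every child in the prevalence outcome.

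Because the Results section reports that pre-post analyses were under way in April 2026, record the change in a dated amendment that says what had been seen by then.

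No new data collection is needed. The costs are a documented late change to the analysis and a smaller n for the main estimate: if 20% fell below the cut-off, the standard error at a given SD would rise by a factor of √(1500/1200) = 1.12. The established-stratum result remains an uncontrolled before-and-after comparison and should be described as such.
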